## 6.6 End of Trial Visit

Patients will be followed 1 month (+/-7 days) after end of treatment for continuing or new adverse events as well as serious adverse events and adverse events of special interest. Patients will be instructed to inform about future occurrence of any chronic clinical disease including hematological, oncological or immunological disease during the following 24 months after study end to monitor long-term safety.

## 6.7 Planned Treatment after End of Trial

There is no planned treatment after end of trial. Parents/caregivers will be instructed to continue therapeutic management according to SOC for all subjects after the end of the trial. The investigator will continue to observe all subjects (also withdrawals) for intolerable (S)AEs until the findings have been clarified or became stable. Currently, there are no data supporting that treatment with sirolimus after the age of 2 years improves cognitive outcomes, so we do not plan to continue administering sirolimus to study participants after the end of the study treatment period. However, if parents/caregivers wish to continue sirolimus treatment, the physician may consider individualized treatment.

## 6.8 Assessments

Informed consent: The informed consent procedure (date, version, agreement) will be documented.

Inclusion/ exclusion criteria: Once all examinations and procedures are completed and laboratory results are returned, the patient's results should be compared to the inclusion/exclusion criteria list (chapters 4.3 and 4.4). If all criteria are met at the start-of-treatment visit (V1) based on the examination findings and laboratory results from the screening visit, the patient can be randomized and receive the study medication, if randomized to the treatment group. The result of the inclusion/exclusion criteria procedure will be documented.

Diagnosis of TSC: Each patient must have a documented diagnosis of TSC according to the 2021 Updated International Tuberous Sclerosis Complex Diagnostic Criteria [58]. The date and criteria of diagnosis will be recorded in the eCRF.

Table 7: Diagnostic Criteria of TSC

Diagnostic Criteria

| Major Criteria                                             | Minor Criteria                  |
|------------------------------------------------------------|---------------------------------|
| Hypomelanotic macules ( $\geq 3$ ; at least 5 mm diameter) | “Confetti” skin lesions         |
| Angiofibroma ( $\geq 3$ ) or fibrous cephalic plaque       | Dental enamel pits ( $\geq 3$ ) |
| Ungual fibromas ( $\geq 2$ )                               | Intraoral fibromas ( $\geq 2$ ) |
| Shagreen patch                                             | Retinal achromic patch          |
| Multiple retinal hamartomas                                | Multiple renal cysts            |
| Multiple cortical tubers and/or radial migration lines     | Nonrenal hamartomas             |
| Subependymal nodule ( $\geq 2$ )                           | Sclerotic bone lesions          |
| Subependymal giant cell astrocytoma                        |                                 |
| Cardiac rhabdomyoma                                        |                                 |
| LAM*                                                       |                                 |
| Angiomyolipomas ( $\geq 2$ )*                              |                                 |

Abbreviations:

LAM = Lymphangiomyomatosis

TSC = Tuberous sclerosis complex

**Definite TSC:** 2 major features or 1 major feature with 2 minor features.

**Possible TSC:** either 1 major feature or  $\geq 2$  minor features.

**Genetic diagnosis:** A pathogenic variant in *TSC1* or *TSC2* is diagnostic for TSC (most TSC-causing variants are sequence variants that clearly prevent TSC1 or TSC2 protein production. Some variants compatible with protein production [e.g., some missense changes] are well established as disease-causing; other variant types should be considered with caution).

\* A combination of the 2 major clinical features LAM and angiomyolipomas without other features does not meet criteria for a definite diagnosis.

Genetic information: Age at genetic diagnosis [months, if applicable], type of investigation [single gene, panel, exome, genome], inheritance [de novo, maternal, paternal, other], Transcript [NM\_], Nucleotide change [c.], Amino acid change [p.], other genetic findings or variants [text].

General parameters: Sex, age [months], height [cm], weight without clothing [kg] and occipital-frontal circumference (OFC) [cm] will be documented at screening and measured at each study visit. Investigations are performed according to routine care and are used in the clinical trial analysis.

Relevant medical history /Current conditions: gestational age at birth [weeks + days], OFC at birth [cm], length at birth [cm], weight at birth [g], complications or abnormalities during pregnancy [infection, amniotic fluid complications, bleeding, placental complications, other (text)], mode of delivery [preterm labor, spontaneous, scheduled induction, scheduled caesarean, unplanned caesarean, other (text)], perinatal complications [respiratory distress syndrome, heart problems, temperature control problems, intraventricular hemorrhage, neonatal seizures, anaemia, metabolic problems, other (text)], history of any major illness or concomitant medical conditions [heart failure, cardiac arrhythmia, deterioration of lung function or pulmonary disease, impairment of gastrointestinal function or gastrointestinal disease, liver dysfunction or disease, active skin or mucosa disorders, active or uncontrolled severe infections, known history of HIV seropositivity or

|                                                                    |                                              |                                |
|--------------------------------------------------------------------|----------------------------------------------|--------------------------------|
| Clinical Trial Code: PROTECT
EU trial number: 2022-502332-39-00 | Trial Protocol
(Version 06; (01.10.2024)) | Page 73 of 110
CONFIDENTIAL |
|--------------------------------------------------------------------|----------------------------------------------|--------------------------------|

other active viral infections, bleeding diathesis, hyperlipidaemia, major surgery or significant traumatic injury within 4 weeks of study entry, active seizures, renal insufficiency, other (text)]. This information, and whether or not the condition is ongoing at IC will be recorded in the eCRF.

Randomisation: Documentation of the randomisation process including date, time and result.

Prior and concomitant ASM therapy: History of all prior anti-seizure medications and current anti-seizure medications [name of active ingredient, date of onset, date of termination, maximum dose in mg/kg of each drug] will be recorded in the eCRF.

Other concomitant therapies: The caregiver will be queried at each visit regarding the use of any medication other than study medication. All current medications [name of active ingredient, date of onset, date of stop, reason for use, daily dose of each drug] will be recorded in the eCRF. All non-medicinal forms of treatment (e.g. physiotherapy) will be recorded in the eCRF [physiotherapy, other (text)].

Physical examination: The physical examination shall be performed by a qualified examiner and must include an evaluation of the entire body on the undressed patient, including: general appearance [good, normal, impaired], level of alertness [normal, impaired], fontanel (if applicable), skin, eyes, ears, nose, throat, lungs, heart, abdomen, back, genitals, lymph nodes, extremities. Abnormal findings are listed [normal / abnormal (text)] in the patient's eCRF. Significant new findings that occur or worsen after informed consent are additionally entered into the eCRF as Adverse Events (AE).

Neurological examination: The neurological examination will be performed by a qualified examiner and must include an assessment of the entire body on the undressed patient, including (if applicable for age of patient): level of consciousness, cranial nerves, passive tone/posture (assessed by observing the supine resting posture, and measured by the resistance to passive movement of the limbs), active motor tone and strength (symmetric and spontaneous movements evaluated in the axial and appendicular musculature in all extremities), deep tendon reflexes (biceps, patellar and ankle), sensory assessment, and primitive reflexes (stepping reflex, grasp reflexes (palmar and plantar), asymmetrical tonic neck reflex (ATNR), galant reflex) [present/absent]. Primitive reflexes will be assessed until Visit 7. Abnormal findings will be listed on the patient's eCRF [normal / abnormal (text)]. Significant new findings that occur or worsen after informed consent are additionally entered into the eCRF as Adverse Events.

Developmental milestones: Developmental screening is done by asking for and observing the patient's abilities in relation to age-appropriate developmental norms and rating developmental progress based on information gained from normative populations, as described by R. Michaelis [96] at 3 months, 6 months, 9 months, 12 months, 18 months and 24 months [97].

Vital signs: Vital signs [pulse rate in beats per minute (bpm), respiratory rate per minute, systolic and diastolic blood pressure in mmHg, and body temperature in °C] will be measured in a supine position and will be repeated at each visit and entered in the eCRF starting at the screening visit until the End-of-trial-visit. Vital signs may be recorded at any time, if medically imperative for clarification of clinical signs and symptoms. Pathological and clinically relevant findings will be documented as (S)AEs.

Seizure diary: A paper seizure diary for the recording of epileptic seizures will be given to the caregivers at the time of inclusion into the study and will be collected at each study visit and replaced by a new seizure diary. Seizure events recorded by the caregivers will be transferred to the eCRF by study personnel. Documentation for each new seizure diary: seizures [yes/no], if yes: frequency of seizures [weekly = 1, daily = 2, more than daily = 3], type(s) of seizure(s) [Focal motor onset (e.g. automatism, atonic, clonic, hyperkinetic, myoclonic, tonic), Focal nonmotor onset (e.g. autonomic, behaviour arrest, cognitive, emotional, sensory), Focal to bilateral (tonic-clonic), Generalized onset motor (e.g. tonic-clonic, clonic, tonic, myoclonic, myoclonic-tonic-clonic,

|                                                                    |                                              |                                |
|--------------------------------------------------------------------|----------------------------------------------|--------------------------------|
| Clinical Trial Code: PROTECT
EU trial number: 2022-502332-39-00 | Trial Protocol
(Version 06; (01.10.2024)) | Page 74 of 110
CONFIDENTIAL |
|--------------------------------------------------------------------|----------------------------------------------|--------------------------------|

myoclonic-atonic, atonic), Generalized onset non-motor (absence, typical or atypical), Unknown onset motor (tonic-clonic), Unknown onset non-motor (behaviour arrest), Infantile spasms], status epilepticus [n], occurrence and duration of worst episode [no status epilepticus = 0, status lasting half hour to 1h = 2, status lasting 1 h or more = 3], response to treatment in last 3 months [complete cessation of seizures = 1, partial cessation of seizures = 2, no improvement in seizures = 3]. At the time of study inclusion, caregivers will be instructed in the use of the seizure diary and informed about different seizure types, including infantile spasms.

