### 2.2 Secondary Objectives and Endpoints

#### 2.2.1 Main Trial

The secondary objectives are adapted to the purpose of this study from the EPISTOP trial, a phase IIb study evaluating the impact of early versus late preventive treatment with vigabatrin on epilepsy in infants with TSC at 2 years of age [14] and will be compared between intervention and control groups:

1. Neuropsychologic outcome at 12 months of age assessed by rater blinded neuropsychologic testing using the cognitive scale on the BSID-III in both groups. Cognitive impairment will be defined as BSID-III cognitive scale score <70 similar to the EPISTOP trial [14].
2. Adaptive behaviour assessed by the Vineland Adaptive Behaviour Scales (VABS-3; digital) at the age of 12 months and 24 months.
3. Evidence for autism spectrum disorder measured at 12 months and 24 months of age by the Autism Diagnostic Observation Schedule (ADOS-2). Suspicion of autism spectrum disorder will be defined as ADOS > 12, similar to the EPISTOP trial [14].
4. Evidence for autism spectrum disorder measured by the Modified Checklist for Autism in Toddlers revised (M-CHAT-R/F).
5. TSC-associated Neuropsychiatric Disorders (TAND) severity assessed by the TAND-L Checklist (German version) at 12 and 24 months.
6. Assessment of seizure frequency and the occurrence/severity of Infantile Spasm measured by seizure diaries, caregiver questionnaires and EEG recordings.
7. Reduction of number and size of cardiac rhabdomyoma and arrhythmia (if present).
8. Reduction of cerebral tumor number and size on cMRI (if present).
9. Adverse events (AE), serious adverse events (SAE) and Adverse Events of Special Interest (AESI), assessed by the *Common Terminology Criteria of Adverse Events (CTCAE, Version 5.0)*.
10. Assessment of laboratory data and vital signs.
11. Assessment of EEG recordings for the occurrence of hypsarrhythmia and epileptiform discharges.
12. Renal changes in abdominal sonography: Volume and size of angiomyolipomas (if present), kidney size, renal pelvis dilation, echogenicity.

|                                                                    |                                              |                                |
|--------------------------------------------------------------------|----------------------------------------------|--------------------------------|

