### 3. Clinical Trial Design

#### 3.1 Overall Trial Design

The clinical trial is planned as a two-armed, randomized, observer-blind, controlled phase IIb clinical trial for children <4 months of age at inclusion.

The treatment group will receive daily oral mTOR inhibitor (sirolimus) therapy in addition to standard of care (SOC), starting within the first 4 months of life. Sirolimus will be continued until the 2nd birthday when neuropsychologic testing will be done. The control group will receive SOC treatment only. Patients randomized to the treatment group will be followed closely with mandatory study visits at screening, start of treatment (V1), titration visits V2-V4 and at an age of 3, 6, 9, 12, 15, 18, 21 and 24 months for safety measures, to adjust sirolimus dosages following PK testing according to prespecified algorithms and to ensure compliance. In case neonates receive their first dose of IMP under the age of 4 weeks (corrected gestational age <4 weeks of life), caregivers will have up to two additional telephone calls by the study personnel up to the end of the 4th week of life. These calls will take place in those weeks where no titration visit takes place. An end-of-trial visit at 25 months of age will monitor safety parameters after end of trial. Subjects randomized to the control group will be treated according to SOC. No placebo will be administered to reduce the number of laboratory examinations at screening, 6 months, 12 months, and 24 months of age to the minimum required to control for laboratory abnormalities unrelated to the study intervention. Mandatory study visits for the control group are at screening and at 3, 6, 9, 12, 15, 18, 21 and 24 months of age. The enrolment in the primary study ends with the end-of-trial visit at age 25 months. Therapy of TSC manifestations according to SOC in both groups will not be affected by the trial. Seizure diaries, use of anti-seizure medications and concomitant medications, adverse events, vital signs (blood pressure, temperature, heart rate), height, body weight, OFC, and physical / neurological exam, and developmental milestones will be assessed at every visit. EEG and abdominal sonography will be done as described in chapter 6. Neuropsychologic testing will be performed at 12 and 24 months of age.

A schematic of the trial design is shown:

Figure 3: Schematic diagram of trial

[figure not shown]

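### The seizure-frequency categories start at weekly, so a child with rarer seizures has no valid code and the frequency part of secondary endpoint 6 cannot reliably separate rare from weekly seizures

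*Protocol*

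**What the plan says.** Secondary endpoint 6 (Protocol Section 2.2.1, repeated in the synopsis) is "Assessment of seizure frequency and the occurrence/severity of Infantile Spasm measured by seizure diaries, caregiver questionnaires and EEG recordings".

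Section 6.8, under the seizure diary, sets out how this is captured. The paper diary "will be collected at each study visit and replaced by a new seizure diary", and "Seizure events recorded by the caregivers will be transferred to the eCRF by study personnel". The per-diary record begins "Documentation for each new seizure diary: seizures [yes/no], if yes" and then gives "frequency of seizures [weekly = 1, daily = 2, more than daily = 3"]. The same entry also records seizure type (with infantile spasms as one type), the number of status epilepticus episodes, the duration of the worst episode, and response to treatment over the last three months.

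On visit spacing, Section 3.1 states: "Mandatory study visits for the control group are at screening and at 3, 6, 9, 12, 15, 18, 21 and 24 months of age". The treatment group follows the same ages and also has titration visits at 14-day intervals (Table 1).

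Section 9.5.1 analyses seizure characteristics, as Section 6.8 defines them, by treatment group and time point.

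**The concern.** A category list should have a place for every child who answers yes to the gate question. This one does not: any seizure during the diary period opens the frequency item, but the lowest answer is weekly. The gap falls where the diary is long relative to the lowest category.

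At stake is the frequency component of a named secondary endpoint. If some sites enter weekly for one isolated seizure and others leave the field blank, the tabulated frequencies mix true weekly seizures, rare seizures and avoidable missing values. The analysis cannot undo this if the count was never entered, and a note in a comment field would not help, because Section 9.3 only lists free text. Section 10.1 also requires the eCRF and the source documents to agree. Weekly, entered for a diary showing one seizure, does not meet that requirement.

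**Working it through.** The plan gives no figure of its own on this point, so there is nothing to reproduce. The check is rate arithmetic and a trace from the endpoint to its analysis.

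**Inputs**
- Categories: weekly, daily, more than daily (Section 6.8).
- Gate: frequency is coded whenever seizures = yes (Section 6.8).
- Diary period: one visit to the next (Section 6.8).
- Visit spacing: three months from month 3 to month 24 (Section 3.1), and 14 days during titration in the treatment group (Table 1).

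**Step 1: length of a diary.** 365.25 / 4 = 91.3 days, and 91.3 / 7 = 13.04 weeks. Visit windows of 7 or 14 days either side change this only slightly.

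**Step 2: rate for n seizures.** Rate per week = n / 13.04. If the site enters weekly, the overstatement is 13.04 / n.

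| Seizures in the diary | Per week | Overstatement if coded weekly |
|---|---|---|
| 1 | 0.077 | 13.0-fold |
| 2 | 0.153 | 6.5-fold |
| 3 | 0.23 | 4.3-fold |
| 6 | 0.46 | 2.2-fold |
| 12 | 0.92 | 1.1-fold |
| 13 | 0.997 | 1.0-fold |

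Counts of about 1 to 12 therefore lie below weekly and have no code of their own. The mismatch is large at the low end and negligible near 12.

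**Step 3: short diaries.** In a 14-day titration diary, one seizure is 1 / 2 = 0.5 per week, which again has no code. Two seizures are 2 / 2 = 1.0 per week, which fits weekly. The gap remains but is narrower.

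**Step 4: width of the lowest code.** The protocol gives no boundary between weekly and daily. Assume that sites use weekly for anything short of daily. Daily seizures over a diary would number about 91, so code 1 could cover roughly 1 to 90 seizures. This span depends on that reading.

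**Step 5: trace to the analysis.** Section 2.2.1 names seizure frequency as an endpoint. Section 6.8 is the only place that turns it into recorded categories, and among its listed fields only status epilepticus has a number of episodes. Section 9.5.1 points back to Section 6.8. No other section adds a lower category or defines seizure frequency differently.

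**The case against.** The strongest reply is that the consequences are limited. Much of it stands.

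- **Nothing forces the weekly code.** A reader might infer that a child with one or two seizures must be recorded as having weekly seizures. Section 6.8 has no rounding rule, and a blank is equally possible. What is shown is a list that is not exhaustive, with two unsatisfactory ways out.
- **Counts may reach the eCRF.** The sentence on transferring seizure events could mean entry event by event, with the codes as a summary. The eCRF and the diary template are not at hand. Even so, the listed fields contain no seizure count, and the analysis is tied to Section 6.8. The endpoint also draws on caregiver questionnaires and EEG, but neither is given a frequency definition.
- **Other items capture part of any effect.** A reader might infer that a real reduction would be invisible, for example a fall from 13 seizures to 1, which is 1 - 1/13 = 92%. The arithmetic is right, but it compares two chosen counts and estimates neither bias nor the number of children affected. Such a fall could appear as partial cessation in the treatment-response item. Prevention or delay of onset would appear in the yes/no item, and prevention of infantile spasms in the type item.
- **Differential coding between arms is not shown.** Trial personnel are unblinded (Section 5.1.2), so it is tempting to suspect that the choice between blank and weekly will differ by group. The documents give no evidence of this and no direction.
- **The status item is weak support.** Its labels run "no status epilepticus = 0, status lasting half hour to 1h = 2, status lasting 1 h or more = 3". A skipped label does not distort a frequency table, and nothing shows that a category is missing. The number of episodes is recorded separately.

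None of these points supplies a valid frequency code for a child with rare seizures.

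**Conclusion.** The point holds for the frequency item. Followed exactly, Section 6.8 gives no correct entry for a child with about 1 to 12 seizures in a three-month diary. The result is either a blank or a weekly code that overstates the rate by up to 13-fold. The frequency component of secondary endpoint 6 therefore cannot reliably separate rare from weekly seizures.

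This rests on two assumptions: that the eCRF holds the fields listed in Section 6.8 and no separate seizure count, and that diaries run the full interval between visits. If event-level counts are in fact entered, the frequency could be derived from them and the remaining task would be to define it that way.

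The reach is limited. It concerns one component of one of twelve secondary endpoints, for which Section 9.5.1 specifies analysis by group and time point but no hypothesis test. The yes/no, seizure-type, infantile-spasm and treatment-response items are unaffected, as are the primary endpoint, its alpha and its power. The protocol gives no distribution of seizure frequency, so the share of children affected is unknown.

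**What to change.** Either of two changes to Section 6.8 and the eCRF closes the gap:

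1. Add a less-than-weekly category below the present lowest one.
2. Enter the seizure count for each diary with the diary's start and end dates, so that a rate can be derived. This is preferable because it also handles the shorter titration diaries and the unclear boundary between weekly and daily.

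For children already enrolled, back-enter the same information from the collected diaries. This should be feasible: Section 6.2 has caregivers instructed in counting seizures and keeping a daily diary, and Section 11.1 requires source data to be archived. If the eCRF already holds event-level entries, state that frequency is derived from them.

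As a minor check, confirm whether label 1 in the status-duration item was left out by mistake.

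The cost is a small eCRF change and some back-entry, which grows with each further visit. Visits, the primary analysis and the sample size do not change.

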### **Rescue medications**

Midazolam (buccally, from 3 months) and rectal diazepam are approved rescue medications for prolonged epileptic seizures. They have anti-seizure effects and they can have sedative effects. Recurrent or chronic use should be avoided, as negative effects on neuropsychological outcome similar to phenobarbital can be expected.

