## 8. Adverse Events

### 8.1 Definitions

#### 8.1.1 Adverse event

According to GCP, an adverse event (AE) is defined as follows: Any unexpected medical occurrence in a subject to whom a medicinal product is administered and which does not necessarily have a causal relationship with this treatment. An AE can therefore be any unfavorable and unintended sign (including an abnormal laboratory finding), symptom, or disease temporally associated with the use of an investigational medicinal product (IMP), whether or not related to the IMP.

An AE may be:

- New symptoms/medical conditions
- New diagnosis
- Changes of laboratory parameters which are considered as clinically significant
- Occurrence of new pathological and clinically relevant findings
- Aggregation of pre-existing symptoms in physical and neurological examinations, vital signs, ECGs, clinical chemistry, haematology etc.

The criteria that should be considered when determining whether an abnormal test finding should be reported as adverse event are as follows:

1. Test result is associated with accompanying symptoms, and/or
2. Test result requires diagnostic testing or medical/surgical intervention, and/or
3. Test result leads to a change in clinical trial dosing outside the protocol-stipulated dose adjustments, or discontinuation from the clinical trial, significant additional concomitant drug treatment, or other therapy, and/or
4. Test result is considered clinically relevant at the discretion of the investigator or sponsor
5. Intercurrent diseases and accidents
6. Worsening of medical conditions/ diseases existing before clinical trial start
7. Recurrence of disease
8. Increase of frequency or intensity of episodic diseases.

A pre-existing disease or symptom will not be considered an adverse event unless there will be an unexpected change in its intensity, frequency or quality. This change will be documented by an investigator (see also above).

Surgical procedures themselves are not AEs; they are therapeutic measures for conditions that require surgery. The condition for which the surgery is required may be an AE. Planned surgical measures permitted by the clinical trial protocol and the condition(s) leading to these measures are not AEs, if the condition leading to the measure was present prior to inclusion into the clinical trial.

In the latter case the condition should be reported as medical history.

AEs are classified as "non-serious" or "serious".

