## 9.5 Secondary Analyses

### 9.5.1 Main Trial Analyses

**All secondary parameters** will be analyzed for the FAS.

BSID-III cognitive scale at the age of 1 year will be analysed similar to the primary endpoint. In addition, the BSID-III cognitive scale and important subscales will be analysed descriptively by group and time point using standard descriptive measures for continuous variables. The VABS total scales, important VABS subscales, ADOS total scales, and important ADOS subscales will be analysed descriptively by group and time point using standard descriptive measures for continuous variables, as well. In addition, for cognitive impairment and autism spectrum disorders at 1 and 2 years of age, 95% CIs will be calculated by treatment group in addition to the relative frequencies using the method of Wilson. The M-CHAT-R/F and TAND will be analysed descriptively by group and time point using absolute and relative frequencies.

The MRI characteristics (as defined in Section 6.8) will be analysed by group and time point, i.e. randomization (last image before randomization) and at 2 years of age  $\pm$  6 months.

Seizure characteristics, EEG characteristics, abdominal sonography characteristics, ECG and echocardiography characteristics (as defined in Section 6.8) will be analysed by treatment group and time point (if applicable).

All **safety parameters** will be analyzed for the SAF. Only treatment emergent-event adverse events will be analysed. Frequencies (number of adverse events & number and percentage of patients with at least one adverse event) will be tabulated according to system organ class and preferred term. One table each will be created showing: all adverse events, all serious adverse events, all adverse events of special interest, all non-serious adverse events, all adverse events leading to death, all adverse events related to the treatment (treated group only), all adverse events by severity. In addition, adverse events and special situations will be analysed by categories defined in the eCRF (number of events & number and percentage of patients with at least one event).

For laboratory values and vital signs, the analyses will be conducted by visit and shift tables comparing all values by visit to the relevant baseline value will be displayed additionally.

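### The seizure diary's treatment-response code pools worsening with no change, and its status epilepticus code is incomplete or misnumbered

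*Protocol*

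**What the plan says.** Protocol section 6.8 (Seizure diary) lists what site staff transfer from each paper diary to the eCRF. Three of its items matter here:

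- Frequency, filled in if there were seizures: "frequency of seizures [weekly = 1, daily = 2, more than daily = 3".
- Status epilepticus, as a count and a code for the worst episode: "status epilepticus [n], occurrence and duration of worst episode". The code values are "no status epilepticus = 0, status lasting half hour to 1h = 2, status lasting 1 h or more = 3".
- Response to treatment over the preceding three months: "complete cessation of seizures = 1, partial cessation of seizures = 2, no improvement in seizures = 3".

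The protocol gives no minimum duration for an episode to be recorded as status epilepticus.

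Section 9.5.1 takes these items as they stand: "Seizure characteristics, EEG characteristics, abdominal sonography characteristics, ECG and echocardiography characteristics (as defined in Section 6.8) will be analysed by treatment group", and by time point where applicable. It names no test and no score for them. Secondary endpoint 6 in section 2.2.1 draws on the same diary: "Assessment of seizure frequency and the occurrence/severity of Infantile Spasm measured by seizure diaries", together with caregiver questionnaires and EEG.

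Outside the diary, section 8.1.1 lists "Increase of frequency or intensity of episodic diseases" among the criteria for reporting an adverse event.

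**The concern.** A response scale that is compared between arms should be able to move in both directions. This one has two values for benefit and none for deterioration. The protocol itself gives a reason to look for deterioration: section 1.3.7.1 describes an earlier randomized sirolimus trial in children with TSC in which an increase in seizure frequency was among the severe adverse events that led to stopping treatment.

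The status code raises a separate doubt. The frequency and response codes in the same item run 1, 2, 3 without a gap, whereas the status code runs 0, 2, 3. Either a category has been dropped or the numbering is a slip, and the text does not show which. If sites resolve this differently, similar episodes will be coded differently.

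Section 9.5.1 ties the analysis to the section 6.8 definitions, so a category that was never collected cannot be restored in the statistical analysis plan.

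**Working it through.** No arithmetic applies. The check is to run possible cases through the code lists and see whether each has exactly one correct value and whether different courses give different codes. The seizure counts and durations below are illustrations, not protocol figures.

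**Response and frequency codes together**

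| Course between two diaries | Frequency code | Response code |
|---|---|---|
| Two a day, falling to weekly | 3 then 1 | 2 |
| Two a day, unchanged | 3 then 3 | 3 |
| Two a day, rising to ten a day | 3 then 3 | 3 |
| Weekly, rising to daily | 1 then 2 | 3 |

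The second and third rows are identical: once a child is at the top frequency value, further worsening shows in neither item. The fourth row shows the limit of the problem. Below the cap, deterioration is visible in the frequency code even though the response code does not register it. Deterioration that takes the form of a new seizure type or more status episodes can also appear in those fields.

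**Adverse event reporting as the other route**

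Section 8.1.1 includes an increase in an episodic disease, so worsening seizures can be reported and would then be tabulated by arm under section 9.5.1. The same section, however, does not count a pre-existing disease as an adverse event unless its intensity, frequency or quality changes unexpectedly. A site may regard worsening epilepsy in TSC as expected. Section 5.1.2 states that trial personnel are not blinded, so that judgement is made with the allocation known. This route therefore covers deterioration in part.

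**Worst-status code**

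| Worst episode | If shorter episodes count as status | If status means at least half an hour |
|---|---|---|
| 10 minutes | n is 1 or more; no duration code fits | n = 0 and code 0, consistent |
| 45 minutes | 2 | 2 |
| Exactly 1 h | 2 or 3 | 2 or 3 |
| 90 minutes | 3 | 3 |

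Under the first reading a category is missing. Under the second the list covers every episode and the absent 1 is only a numbering gap. Under both, the two upper categories overlap at one hour.

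**Link to the endpoints**

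Endpoint 6 names seizure frequency and infantile spasms, not status duration or treatment response. What brings those two items into the arm comparison is the reference to section 6.8 in section 9.5.1.

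**The case against.** The best defence has four parts.

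1. Value 3 is literally true of a child who gets worse, because there was no improvement. This stands. What is lost is resolution; the entry is not false.
2. The shortest duration category starts at half an hour, which fits an unstated half-hour threshold. On that reading no short episode is miscoded. This also stands as a possibility, and it is why the point on short episodes can only be conditional. Section 5.3 does speak of "approved rescue medications for prolonged epileptic seizures", but a prolonged seizure stopped by rescue treatment need not be status epilepticus, so that passage does not show that short status episodes will be common.
3. Worsening is recorded elsewhere: in the frequency code, the seizure types, the status count and adverse events. Section 8.1.2 also gives seizures without hospitalization as an example of events usually considered serious, and the seizure increase in the earlier sirolimus trial was itself reported as an adverse event. This stands in part. It defeats any claim that harm to seizure control could not appear in the trial's data at all, but the frequency cap and the condition that the change be unexpected leave a gap.
4. The overlap at exactly one hour matters little for times estimated by caregivers, and section 9.5.1 plans no score that uses the spacing of the codes. Both are fair, and they keep the point small.

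A reader might infer that short status episodes and deteriorations are being recorded wrongly, or that a definite share of status episodes will be lost. The protocol supports neither: it sets no minimum duration and gives no distribution of episode lengths.

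**Conclusion.** The point holds in a limited form. The response code pools worsening with no change, and for a child already at the top frequency value the two items together cannot show further deterioration. The arm comparison of these items can therefore show benefit but not always harm. The status code has overlapping limits at one hour and is either missing a category or misnumbered; which of these applies depends on a definition the protocol does not give.

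The size cannot be put as a number, because the protocol reports neither how many children are expected to have more than daily seizures nor how long status episodes last. The consequence is confined to descriptive secondary seizure data. The primary BSID-III analysis, the sample size and the power do not use these items. The conclusion assumes that the eCRF follows the lists in section 6.8 as printed; if it already holds further values, only the protocol text needs correcting.

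**What to change.** 1. Response code: add a separate value for worsening, and one for not applicable where no treatment was given in the period. The absence of seizures seems already to be covered by the yes/no question that opens the item.
2. Status code: state the definition of status epilepticus used for recording and reconcile the list with it. If shorter episodes are counted in the number of episodes, add the missing duration category; if not, renumber. The choice of definition belongs to the clinical investigators.
3. Make the one-hour limit exclusive, so that an episode of exactly one hour falls in one category only.

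The cost is a small eCRF change and re-coding of any entries already made. Earlier diaries may lack the detail to separate worse from unchanged, so early entries may have to stay in the pooled value and be reported as such; the sooner the change is made, the fewer there will be.
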